#### Data analysis

Following the completion of each interview, the two interviewers summarize the results for that interview. The summaries include the following information: (1) Overall themes and behavioral observations; (2) General difficulties in completing the PCSS, along with detailed descriptions of each difficulty; (3) Difficulties in answering specific questions, along with detailed descriptions of those difficulties; and (4) Responses to specific interview topics of interest [comprehension and clarity of each item, interpretation of the concept of bother, relevance of the response scale(s) and their ease of use, and understanding of the recall period]. The interviewer also notes caregiver-proxy or child recommendations for phrasing adjustments to the PCSS to improve comprehension or clarity, and documents elements of interview quality (e.g., length of the interview, any technical difficulties, child and caregiver engagement in the interview process, and relevant developmental, clinical or environmental contextual factors). The Interviewer Case Report Form (CRF; see Supplementary Table 1) was developed to code and summarize each interview. The CRF includes a place to enter the child and caregiver-proxy responses to PCSS items, capture self-reported and behavioral indicators of comprehension difficulties, summarize item-by-item comprehension as determined jointly by the two interviewers, and document the child’s verbatim statements rephrasing the item or describing its meaning in their own words that indicate comprehension or non-comprehension. While the digital recordings are not transcribed, interviewers review the recording after the interview is concluded to confirm coding or improve the capture of verbatim statements reflecting comprehension or misunderstanding.

Data are analyzed after every five interviews, and cumulative item-by-item determinations of both comprehension and saturation, stratified by age band, are documented in a coverage and saturation matrix (Kerr et al., 2010; Tomlinson et al., 2016; Meadows, 2021). Each transcript is mapped back to each PCSS item and a cumulative summary of the findings for each item and next steps (i.e., revise and retest, comparatively test a revision, continue testing, saturation achieved, and eliminate item from item pool) is constructed for each item and organized in Microsoft Excel. This approach also ensures that all PCSS items receive a comparable extent of probing across interviews within each age band and identifies the timepoint at which no new information about an item is being generated by the interviews.

Each PCSS item is debriefed with at least five children within each age band. Cognitive interviews are normally based on intensive interviewing in relatively small samples (Willis et al., 2005; Willis, 2005, 2015). Approximately 5–8 participants per item and per age group is a general rule of thumb to achieve saturation with cognitive interviews (Kerr et al., 2010; Hennink et al., 2017) since the type of logical and structural problems that we wish to identify are relatively independent of sample size (Miller et al., 2014). Symptom terms eliciting confusion or demonstrating misinterpretation by three or more respondents within an age band are considered for revision. Interview scripts are slightly refined to accommodate these changes to PCSS items.

When an item has been revised, it remains in the item pool for debriefing until it has been determined to be acceptably comprehended. Criteria or thresholds for concluding that a PCSS item is acceptably comprehended include resolution of any observed barriers to comprehension or clarity, achievement of an item-level comprehension rate (as demonstrated by the child correctly rephrasing the item in their own words) of 80% within each age band (Miller et al., 2014). An *a priori* stopping rule for concluding that comprehension of the PCSS by 5–7 year old cannot be achieved was established as the point at which 30% or more of the PCSS items are misunderstood and unable to be correctly rephrased. Study reporting will be guided by the Standards for Reporting Qualitative Research (SRQR) checklist (O'Brien et al., 2014) and the Consolidated Criteria for Reporting Qualitative Research (COREQ; Tong et al., 2007; Buus and Perron, 2020). SPSS and Excel are used to support data management and analysis.

### Phase 2: evaluate the measurement properties of the PCSS

#### Design and sample

In the second phase of this study, a cohort of 120 child and caregiver-proxy dyads, stratified by child age, will be recruited at 13 centers in the United States and Canada. Eligibility criteria are the same as those for the qualitative phase (children ages 5–17, with a diagnosis of cGVHD and currently receiving systemic immunosuppression or have had their immunosuppression tapered to discontinuation within the past 12 months). Participants in phase 1 of the study will also be approached, evaluated for eligibility, and if willing to participate, will be consented and enrolled.

#### Data collection procedures

After enrollment, the child participant and their caregiver-proxy will be provided with their own unique secure electronic link to independently complete the study measures [PCSS, PedsQL general (Varni et al., 2007c) and transplant modules (Lawitschka et al., 2014), and LSS; corresponding to their role (child or caregiver-proxy) and age band (5–7; 8–12, and 13–17 years); see Table 3 for a summary of the assessment schedule]. To examine test-re-test reliability, both the child and their caregiver-proxy will complete a second PCSS within 24–48 h of their initial completion of the measures (T2). To explore the responsiveness of the PCSS, study participants will complete the PCSS and PedsQL (general and transplant module) approximately 3 months (T3) after enrollment. They will also be asked to indicate whether their cGVHD symptoms have worsened, are unchanged, or have improved. Caregiver-proxy participants may assist their younger child (ages 5–7 and 8–12 as warranted) in completing this global assessment of change in cGVHD symptoms. Respondents ages 13–17, and their caregiver-proxies will also complete the LSS at all three timepoints. The measures are described in more detail in Supplementary Table 2.

**Table 3 tab3:** Summary of patient-reported outcomes by timing of assessment and age group (Phase 2).

Study assessments	Enrollment/Baseline	24–48 h after baseline	3 months after baseline

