## Objectives and specific aims

The overall objective of this two-phase multi-center study is to develop a psychometrically valid pediatric cGVHD Symptom Scale (PCSS; including both a child and a caregiver-proxy version), as a counterpart to the LSS, to accurately and precisely capture cGVHD symptom bother in pediatric transplant survivors.

This objective will be addressed through four specific aims:

Evaluate the comprehensibility, clarity, acceptability, and ease of judgment of three age appropriate versions of the PCSS items and response choices with children across the developmental spectrum, and with their caregiver-proxies.Evaluate the validity (concurrent validity, known-groups validity, and validity of the response scales), test–retest reliability, responsiveness, minimally important difference (MID), and the acceptability and time required to complete the PCSS (both pediatric and caregiver-proxy versions).Determine the youngest age at which the PCSS can be comprehended.Examine concordance between the PCSS and the LSS in order to establish the youngest age at which the LSS validly captures cGVHD symptom bother.

Guided by developmental science and expert recommendations for the development and testing of patient-reported outcome measures (Riley, 2004; Klassen et al., 2010; Mokkink et al., 2010; Patrick et al., 2011; Arbuckle and Abetz-Webb, 2013; Coyne et al., 2016; Tomlinson et al., 2016; Pinheiro et al., 2018; Terwee et al., 2018; Leahy and Steineck, 2020; Coombes et al., 2021, 2023; Rothmund et al., 2023), this multi-site study will achieve its aims in two phases. An overview of the two phases of the study is provided in Table 1.

**Table 1 tab1:** Overview of the two phases of the mixed-methods study.

Phase	Participants	Method	Inclusion criteria	Exclusion criteria	Projected sample size	Timepoints of data collection	Main objective

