**Caregiver-proxy (all age groups)**			
Caregiver-proxy PCSS	X	X	X
Caregiver Peds QL Proxy	X	X	X
Caregiver Peds QL Transplant Module Proxy	X	X	X

^*^There is no child report version of the Peds QL Stem Cell Transplant Module validated for children ages 5–7. Caregivers of children ages 5–7 will complete the Caregiver Peds QL Transplant Module Proxy.

Child participants and their caregiver-proxies will receive phone and/or e-mail reminders to log into their unique survey interface to complete required study measures. To minimize missing data, completeness will be monitored prospectively by the study team. Back-up data collection procedures will be implemented for participants who do not complete their scheduled measures.

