##### Responsiveness to change

To explore the responsiveness of the PCSS, study participants will be categorized into three groups based on responses to a question about their global impression of symptom change from baseline to 3 months (Coon and Cook, 2018). Within each group (no change, worsened, and improved), the total PCSS score will be compared used a paired *t*-test. The standardized response mean will be computed as the mean change scored divided by the standard deviation of the change scores within each change category (worsening vs. no change vs. improvement). Values greater than 0.8 will be considered large and values between 0.5 and 0.8 will be considered moderate. Subsequently the change in total score will be investigated using analysis of covariance in which the T1 score is a covariate and change in symptom severity (worsening vs. no change vs. improvement) is a factor in modeling the T2 rating. Lastly, change scores will be modeled using a generalized linear regression model. cGVHD severity scores and change in PedsQL physical function scores will be incorporated into this model in confirmatory analysis. These various approaches to examining responsiveness to change will be triangulated to preliminarily propose clinically meaningful thresholds for change at the individual and group level (Trigg and Griffiths, 2021).

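### The three-level change question at 3 months cannot separate small from large change, so a minimally important difference read from it is liable to be too large; whether caregivers give their own rating is unclear

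*Protocol article*

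**What the plan says.** Objectives and specific aims, Aim 2, lists among the properties to be evaluated "responsiveness, minimally important difference (MID), and the acceptability and time required to complete the PCSS (both pediatric and caregiver-proxy versions". The MID is therefore promised for both forms.

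Under Phase 2, Data collection procedures, "study participants will complete the PCSS and PedsQL (general and transplant module) approximately 3 months (T3) after enrollment". The next sentence describes the change rating: "They will also be asked to indicate whether their cGVHD symptoms have worsened, are unchanged, or have improved". It is followed by: "Caregiver-proxy participants may assist their younger child (ages 5–7 and 8–12 as warranted) in completing this global assessment of change in cGVHD symptoms".

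Responsiveness to change sorts participants by this rating into no change, worsened and improved. Those groups are used for paired t-tests, standardized response means and an analysis of covariance. A further regression of change scores brings in cGVHD severity and change in PedsQL physical function. The results are combined to "preliminarily propose clinically meaningful thresholds for change at the individual and group level".

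Table 3 lists a global self-assessment in each of the three child blocks, at baseline and at 3 months. The block headed "Caregiver-proxy (all age groups)" lists the proxy PCSS and the two proxy PedsQL forms, and no global rating.

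**The concern.** An anchor-based MID needs a group whose change was small but noticeable. A question with one category for all improvement and one for all worsening does not supply it: each category mixes small and large change, and its mean is an average change. This is settled when the data are collected. If the size of change is not asked at 3 months, it cannot be recovered from this item.

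An MID that is too large would lead later trials using the PCSS to dismiss small benefits that patients notice. Two further matters affect what the rating can support. The proxy form needs a change rating from the caregiver, and the text and Table 3 do not agree on whether one is collected. The child's own rating may also be given with help from the caregiver who completes the proxy PCSS.

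**Working it through.** The documents give no MID, no expected distribution of the change rating and no standard deviation of change, so there is no planned figure to reproduce. The calculations below use assumed inputs and show direction and plausible range only.

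**1. Pooled group against the minimally improved group.** Let *p* be the share of improvers whose change is more than minimal, and *k* their mean change relative to minimal change. The ratio of the pooled mean to the minimal mean is

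R = (1 − p)·1 + p·k = 1 + p(k − 1).

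| k | p = 0 | p = 0.2 | p = 0.4 | p = 0.6 |
|---|---|---|---|---|
| 1.5 | 1.0 | 1.1 | 1.2 | 1.3 |
| 2 | 1.0 | 1.2 | 1.4 | 1.6 |
| 3 | 1.0 | 1.4 | 1.8 | 2.2 |

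For p from 0.2 to 0.6 and k from 1.5 to 3, R runs from 1.1 to 2.2. It is 1.0 if nobody changes more than minimally (p = 0) or if k = 1.

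**2. Latent-normal check.** Perceived change and PCSS change are taken as standard normal with correlation 0.3, 0.5 or 0.7. A child counts as improved above a lower cut-off, and as minimally improved between the lower and an upper cut-off. For cut-off pairs (0.5, 1.0), (0.5, 1.5) and (0.75, 1.5), the simulated ratio ranges from 1.24 to 1.56. It hardly depends on the correlation, which scales both means alike: at correlation 0.5 with cut-offs 0.5 and 1.0 the means are 0.570 and 0.366, ratio 1.56.

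**3. The opposing error.** If a share *m* of those rated improved had no real change, the ratio becomes (1 − m)R. With p = 0.4 and k = 2 (R = 1.40):

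- m = 0.1: 0.9 × 1.40 = 1.26
- m = 0.2: 0.8 × 1.40 = 1.12
- m = 0.3: 0.7 × 1.40 = 0.98

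The excess vanishes at m = 1 − 1/1.40 = 0.29.

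**4. Caregiver assistance.** Table 1 plans 40 dyads aged 5–7 and 40 aged 8–12. Assistance is allowed in both bands, so at most 40 + 40 = 80 of 120 child ratings could be assisted. This is a ceiling, not an expected number.

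**5. Caregiver rating: text against Table 3.** The text asks study participants for the rating and then speaks of caregiver-proxy participants, so caregivers could be included. Table 3 gives them no such row. But its caregiver block is incomplete: the text assigns the Lee scale (LSS) to caregivers of 13–17 year olds at all three timepoints, and the block omits it. The global item in the child blocks is also marked at baseline, where change since baseline cannot be rated, so it may not be the change question. Neither place settles the matter.

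**The case against.** The strongest reply is that this is a condensed article. The supplementary table describing the measures is not shown, and sorting answers into three groups would also fit a finer item collapsed for analysis. If the full protocol holds such an item, the main point falls away. As described, though, the question has three answers and the analysis uses the same three groups.

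Second, nothing defines the MID as the mean of the whole improved or worsened group. Several approaches are to be combined, and the thresholds are called preliminary. A reader might infer that the plan does overstate the MID; the documents do not support that, and misclassified ratings pull the other way. The risk remains, because the t-tests, standardized response means and analysis of covariance share the three-level grouping. Clinical severity and PedsQL change enter only the last model, and neither is a respondent's rating of a small but noticeable change.

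Third, a reader might infer that caregivers have no change rating, or that the proxy form has no anchor at all. Neither is established. The wording may include caregivers, Table 3 is incomplete, and proxy PedsQL change and cGVHD severity are available as other anchors.

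Fourth, a reader might infer that caregivers complete the child's rating. The text says only that they may assist, where warranted, at ages 5–7 and 8–12. That makes the rating less independent of the caregiver; it does not by itself raise the MID.

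**Conclusion.** The point holds in a limited form. An MID is promised for both forms, and the only change rating described cannot separate small from large change. An MID taken from a whole improved or worsened group is liable to be too large.

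The size is not determined by the documents. Under the assumed inputs the ratio to minimal change is about 1.1 to 2.2 by formula and 1.24 to 1.56 by simulation. It is near 1 if few children change more than minimally, or, in the example with p = 0.4 and k = 2, if about 30% of improved ratings are wrong.

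Whether caregivers give their own change rating is unresolved between Data collection procedures and Table 3. Caregiver help with the child's rating, possible for up to 80 of 120 children, is a matter of independence and not a source of upward bias. The change is a cheap improvement, best made before Phase 2 data are collected.

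**What to change.** - **Graded item.** At 3 months, use five levels (a lot worse, a little worse, same, a little better, a lot better) for ages 8–17 and for caregivers, who already answer the PCSS on five points. Keep three levels for ages 5–7.
- **Analysis.** Collapse to three levels for the tests planned under Responsiveness to change. Use the two *a little* groups as the primary anchor for the preliminary MID.
- **Caregiver rating.** Schedule an explicit caregiver change rating at 3 months as the anchor for the proxy PCSS, and bring Data collection procedures and Table 3 into agreement.
- **Assistance.** Record whether the child was helped, and repeat the analysis in unassisted children.

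**Cost.** Changed response options, one caregiver item and one assistance flag. The planned three-group tests are kept. The *a little* groups will be small and the MID intervals wide. If 20% (assumed) of the 80 children aged 8–17 choose *a little better*, that is 16 children and a 95% half-width of 1.96/√16 = 0.49 standard deviations of change. For 20% of 120 caregivers (24) it is 1.96/√24 = 0.40. A pooled improved group of 30% of 120 children (36) would give 1.96/√36 = 0.33, but for a different quantity. The 5–7 band will not contribute a graded anchor from the child.

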**Child participant age 5–7 years***			
Pediatric cGVHD symptom scale (PCSS)	X	X	X
Peds QL generic module	X		X
Global self-assessment of cGVHD	X		X
**Child participant age 8–12 years**			
Pediatric cGVHD Symptom Scale (PCSS)	X	X	X
Peds QL Generic Module	X		X
Peds QL Transplant Module	X		X
Global Self-Assessment of cGVHD	X		X
**Child participant ages 13–17 years**			
Pediatric cGVHD Symptom Scale (PCSS)	X	X	X
Lee cGVHD Symptom Scale	X	X	X
Peds QL Generic Module	X		X
Peds QL Transplant Module	X		X
Global Self-Assessment of cGVHD	X		X
**Caregiver-proxy (all age groups)**			
Caregiver-proxy PCSS	X	X	X
Caregiver Peds QL Proxy	X	X	X
Caregiver Peds QL Transplant Module Proxy	X	X	X

^*^There is no child report version of the Peds QL Stem Cell Transplant Module validated for children ages 5–7. Caregivers of children ages 5–7 will complete the Caregiver Peds QL Transplant Module Proxy.

Child participants and their caregiver-proxies will receive phone and/or e-mail reminders to log into their unique survey interface to complete required study measures. To minimize missing data, completeness will be monitored prospectively by the study team. Back-up data collection procedures will be implemented for participants who do not complete their scheduled measures.

#### Statistical analysis

The primary objective of the second phase is to quantitatively evaluate the test–retest reliability, construct validity, responsiveness, and the acceptability and time required to complete the PCSS (in both pediatric and caregiver-proxy versions). STATA software will be used to support data management and analysis.

##### Reliability

For test–retest reliability, we will examine the level of agreement between total PCSS score at T1 and T2 using the Intraclass Correlation Coefficient (ICC) in all respondents, within 3–5 days of their initial completion. We will evaluate at T2 if by child and caregiver-proxy report the child remains in stable health and with stable symptoms of cGVHD (Qin et al., 2019). The ICC will be computed based on a two-way, mixed effects analysis of variance model (Shrout and Fleiss, 1979; Liljequist et al., 2019). ICC ≥ 0.70 will be interpreted as demonstrating adequate test–retest reliability.

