Currently receiving systemic treatment for cGVHD (including phototherapies), or has tapered systemic therapy for cGVHD to discontinuation within the past 12 months					Children age 8–12 years: *N* = 40 patient-caregiver dyadsChildren age 13–17 years: *N* = 40 patient-caregiver dyads	T2 (24–48 h after enrollment)T3 (3 months after enrollment)	Congruence between symptom ratings provided by child participants and their caregiver-proxies will be explored.In subjects ages 13–17, we will also compare responses on the PCSS with those from the LSS, to determine the youngest age at which adolescents respondents can comprehend the LSS.				
English speaking											
Absence of severe cognitive or psychiatric disability that would impair the child’s capacity for participation or completion of study related procedures, in the judgment of the investigators								
Caregiver-proxies of participating children		Age older than 18 years						
		Caregiver-proxy of participating subject						
		Able to speak, read, and write English						

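### The retest interval for the test–retest ICC is stated two ways (24–48 h and 3–5 days), and the planned T2 stability report has no item in Table 3 and no stated role in the ICC

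*Protocol article*

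**What the plan says.** Test–retest reliability is part of the primary objective of Phase 2 (Statistical analysis), with an ICC of at least 0.70 taken as adequate (Reliability).

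The timing of the retest is given in four places:

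- Table 1, Phase 2 timepoints: "T2 (24–48 h after enrollment".
- Phase 2, Data collection procedures: child and caregiver-proxy "will complete a second PCSS within 24–48 h of their initial completion of the measures (T2".
- Table 3, column heading: "24–48 h after baseline".
- Statistical analysis, Reliability: agreement between T1 and T2 total scores is examined "using the Intraclass Correlation Coefficient (ICC) in all respondents, within 3–5 days of their initial completion".

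On stability, the sentence after the ICC definition reads, in part, "We will evaluate at T2 if by child and caregiver-proxy report the child remains in stable health", and goes on to cover stable cGVHD symptoms. In Table 3 the row "Global self-assessment of cGVHD" is marked at baseline and 3 months for each child age group, not at 24–48 h, and the caregiver block has no such row. The data collection text describes the worsened/unchanged/improved question with the 3-month assessment. The Discussion names clinical stability as relevant to interpreting test–retest reliability.

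**The concern.** Three statements give one retest window and the analysis section gives another, for the same pair of measurements. The mismatch is not a matter of different starting points, because the data collection text and the Reliability section both count from initial completion of the measures.

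The interval is part of what a test–retest ICC means. A short gap leaves more room for remembered answers, and a longer one leaves more room for real change. A reader of the eventual ICC needs to know which gap it refers to, and an analyst needs one rule for which retests count.

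The stability report is a second loose end in the same section. A test–retest ICC is meant to reflect measurement error in people who have not changed. The section plans to find out who is stable and then, as worded, computes the coefficient in everyone. A stability answer that is not collected at T2 cannot be reliably reconstructed later, so this is best settled before Phase 2 data collection.

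**Working it through.** The article states no sample size, power or precision for the ICC, so there is no figure of its own to reproduce. The check has three parts.

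**1. The two windows in hours**

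- Schedule (Table 1, Table 3, data collection text): 24 to 48 h.
- Analysis (Reliability): 3 × 24 = 72 h to 5 × 24 = 120 h.
- Overlap: max(0, min(48, 120) − max(24, 72)) = max(0, 48 − 72) = 0 h. The gap between the windows is 72 − 48 = 24 h.

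If 3–5 days is an interval, a retest done on schedule falls outside it. If it is an outer limit, an on-schedule retest qualifies, but a retest on day 4 is then late under the data collection text and valid under the Reliability section. Neither reading makes the two statements agree.

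**2. Overlap of the recall periods**

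The PCSS asks about the past month (Phase 1, Design, sample, and setting). Taking a month as 30 days (assumption), overlap = (30 − gap)/30:

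| Gap | Overlap |
|---|---|
| 1 day | 29/30 = 97% |
| 2 days | 28/30 = 93% |
| 3 days | 27/30 = 90% |
| 5 days | 25/30 = 83% |

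These figures show how the two windows differ. They do not translate into an amount of ICC inflation.

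**3. Effect on the ICC of including respondents who changed**

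Assumptions, none of them from the article: T1 variance is 1; r is the ICC in stable respondents; a share u truly changes, with mean-zero change unrelated to the T1 score and with SD k in units of the T1 SD. The T2 variance is then 1 + u·k², and the ICC is approximately covariance over average variance:

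ICC = r / (1 + u·k²/2)

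| r | u | k = 0.5 | k = 1 |
|---|---|---|---|
| 0.80 | 5% | 0.795 | 0.780 |
| 0.80 | 10% | 0.790 | 0.762 |
| 0.80 | 20% | 0.780 | 0.727 |
| 0.80 | 30% | 0.771 | 0.696 |
| 0.75 | 10% | 0.741 | 0.714 |
| 0.75 | 20% | 0.732 | 0.682 |

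For example, r = 0.80, u = 0.20, k = 1 gives 0.80 / 1.10 = 0.727.

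Setting the ICC to 0.70 gives u·k² = 2(r/0.70 − 1). With k = 1, that is a share of about 29% for r = 0.80 and about 14% for r = 0.75. The criterion is missed only when many respondents change and the change is large.

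**The case against.** Several parts of the opposing case stand.

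- **A T2 stability question is planned.** A reader might infer from Table 3 that none is scheduled. The Reliability section says otherwise, and Table 3 is a summary that is visibly incomplete: the data collection text has caregivers of 13–17-year-olds complete the LSS at all three timepoints, yet the caregiver block has no LSS row. A missing row does not show that the item is not collected. What remains is that the table omits an item the text promises.
- **On-schedule retests are not necessarily lost.** A reader might conclude that none would count. That holds only if 3–5 days is an interval. Nor is there support for saying that sites would not know when to send the link, since every operational statement says 24–48 h.
- **It is not stated that unstable children stay in.** "All respondents" in the plan's sense may mean both reporter types and all age bands, and an exclusion rule may sit in the full protocol or analysis plan, which are not shown.
- **The bias is downward.** Keeping respondents who changed makes the criterion harder to meet, so it would not create a false claim of adequate reliability. Changes of 1 SD are also hard to credit over a gap in which the recall periods overlap by 93–97%.

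The conflict over the interval survives all of this, because it lies between statements in the article and is not something left to another document. The stability point survives in a smaller form: the text as written specifies everyone, plans a stability report, and does not connect the two.

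**Conclusion.** The test–retest interval is contradictory on the face of the article: 24–48 h in three places and 3–5 days in the section that defines the ICC. This is more than a clerical slip, because it governs a primary Phase 2 property with a fixed criterion. The finding needs no assumption, and it holds whether 3–5 days is read as an interval or as an outer limit.

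The stability point is secondary. The planned T2 report has no item in Table 3 and no stated role in an ICC specified for all respondents. Its numerical effect is illustrative only: in the cases shown for a stable ICC of 0.80, the reading runs from 0.795 (5% changing, SD 0.5) to 0.696 (30% changing, SD 1), always downward. The documents give no share or size of change. They do not support the claim that reliability will be misjudged against 0.70, only that the definition should be settled.

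**What to change.** 1. Choose one retest window, with one starting point, and use it in Table 1, Table 3, Data collection procedures and Reliability. Say whether it is an interval or an upper limit.
2. Show in Table 3, at T2, the stability item that the Reliability section promises, for both child and caregiver-proxy.
3. Compute the primary ICC in respondents reported stable and retested within the window, and give the ICC in all respondents as a sensitivity analysis. Naming which is primary is a design choice, but this order matches the purpose of asking about stability.

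The cost is wording in four places, at most one additional T2 item if it is not already on the form, and a small loss of retests from respondents reported unstable, who still contribute to the sensitivity analysis.

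### The test–retest ICC does not say consistency or absolute agreement; in the form usually computed from the named model, a systematic T1–T2 shift would not count against the 0.70 mark

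*Protocol article*

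**What the plan says.** The Reliability subsection of the phase 2 statistical analysis states the target: "we will examine the level of agreement between total PCSS score at T1 and T2". It then gives the model, "The ICC will be computed based on a two-way, mixed effects analysis of variance model", and the decision rule, "ICC ≥ 0.70 will be interpreted as demonstrating adequate test–retest reliability". It does not say whether the ICC is for consistency or absolute agreement, or whether it refers to a single measurement or an average.

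One accompanying check is described: "We will evaluate at T2 if by child and caregiver-proxy report the child remains in stable health and with stable symptoms of cGVHD". Neither that subsection nor any other describes a T1–T2 mean difference, a paired test on the retest scores, or limits of agreement. The paired *t*-test under Responsiveness to change concerns baseline to 3 months, within categories of self-rated change.

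Test–retest reliability is the first property listed in the primary objective of phase 2.

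**The concern.** In a two-way mixed-effects layout, occasion (T1, T2) is a fixed effect. The single-measurement ICC usually computed from it compares between-child variance with residual variance after the occasion means have been removed. If every child scored lower by the same amount at the second completion, that coefficient would not move. It describes whether children keep their relative positions, whereas the stated target is agreement between the two scores.

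The reported-stability check does not close this gap, because it concerns health and symptoms and not the score. In children reported as stable, a mean shift would more plausibly be an artefact of repeat completion, and so should count against reliability.

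The scale is meant to measure change. The responsiveness analysis uses within-group mean change and standardized response means, and is to inform thresholds for meaningful change. A repeat-completion shift that persisted to 3 months would enter those means directly.

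**Working it through.** The article gives no power or precision figure for the ICC, so there is none to reproduce.

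**Inputs.** From the article: k = 2 occasions, n = 120 dyads, mark 0.70. Assumed, because the documents give neither a shift nor an SD: within-occasion variance 1, a uniform mean shift of *d* SD between T1 and T2, and a true consistency ICC *C* between 0.75 and 0.90.

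**Formulas.** Let MSR, MSC and MSE be the mean squares for children, occasions and residual.

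- Consistency, single measurement: (MSR − MSE) / (MSR + (k − 1)MSE).
- Absolute agreement, single measurement: (MSR − MSE) / (MSR + (k − 1)MSE + k(MSC − MSE)/n).

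Only the second contains MSC, the term that carries a mean shift.

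**Population values for k = 2.** The child variance is *C* and the residual variance 1 − *C*. So MSR = 1 + *C* and MSE = 1 − *C*, which gives MSR − MSE = 2*C* and MSR + MSE = 2. Also MSC − MSE = n*d*²/2, so k(MSC − MSE)/n = *d*². Therefore:

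- consistency ICC = 2*C*/2 = *C*, whatever *d* is;
- absolute-agreement ICC = 2*C*/(2 + *d*²) = *C*/(1 + *d*²/2).

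**Results.**

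| Shift *d* (SD) | 1 + *d*²/2 | *C* = 0.75 | *C* = 0.80 |
|---|---|---|---|
| 0 | 1.000 | 0.750 | 0.800 |
| 0.2 | 1.020 | 0.735 | 0.784 |
| 0.3 | 1.045 | 0.718 | 0.766 |
| 0.5 | 1.125 | 0.667 | 0.711 |
| 0.8 | 1.320 | 0.568 | 0.606 |

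**Shift at which the absolute form reaches 0.70.** Solving gives *d* = √(2(*C*/0.70 − 1)): 0.38 SD for *C* = 0.75, 0.53 SD for *C* = 0.80 and 0.76 SD for *C* = 0.90.

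**Chance of meeting the mark.** Simulated with n = 120 and 4,000 replicates per setting:

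| True *C* | Shift (SD) | P(consistency ICC ≥ 0.70) | P(absolute ICC ≥ 0.70) |
|---|---|---|---|
| 0.75 | 0 | 0.87 | 0.87 |
| 0.75 | 0.3 | 0.86 | 0.65 |
| 0.75 | 0.5 | 0.87 | 0.23 |
| 0.80 | 0.3 | 0.995 | 0.95 |
| 0.80 | 0.5 | 0.99 | 0.61 |
| 0.80 | 0.8 | 0.996 | 0.01 |

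**Link to responsiveness (illustration).** With equal variances, the SD of change in stable children is √(2(1 − *C*)). A pure 0.5 SD shift that persisted to 3 months would give a standardized response mean of 0.5/0.632 = 0.79 at *C* = 0.80 and 0.5/0.707 = 0.71 at *C* = 0.75. Both lie in the article's moderate band of 0.5 to 0.8, while a consistency ICC at either value meets 0.70.

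**The case against.** The strongest reply is that the article never says it will use the consistency form. A two-way mixed model also has an absolute-agreement form, and the only word bearing on the choice, *agreement*, points to it. This stands. A reader might infer that the stated target and the stated model conflict, and that the 0.70 mark will be applied to the more lenient coefficient. The text does not support that: it leaves the choice open.

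Second, an article may leave such sub-options to the full protocol or analysis plan, which is not shown. This has force for the confidence interval and the mean difference taken alone. It has less for the form of the ICC, because the article itself fixes target, model and pass mark, and what the pass mark means depends on the missing choice.

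Third, nothing in the design specifically predicts a large shift. The retest follows within days, the recall period is one month so the two windows nearly coincide, and stability is asked about at T2. That is fair. It makes true change unlikely but does not rule out a repeat-completion effect.

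Fourth, the self-rated no-change group is to have its mean change tested at 3 months. This is a partial safeguard: it could reveal drift, but at a different interval and outside the reliability criterion.

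**Conclusion.** The point holds as a conditional one. The ICC is under-specified against its own stated target. If it is computed in the usual consistency form, the 0.70 mark cannot register a systematic T1–T2 shift, and nothing else described for the retest would show one. It is not established that the plan uses the wrong coefficient.

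The size depends wholly on an assumed shift. Up to about 0.2–0.3 SD the two forms differ by only 0.015 to 0.034 at consistency ICCs of 0.75 to 0.80. From roughly 0.4–0.5 SD the conclusion can change when the consistency ICC is near 0.75; at 0.80 the population value crosses 0.70 only above about 0.53 SD. A reader might take a consistency ICC of exactly 0.70 as proof that small shifts turn a pass into a fail. That case sits on the cut, where any shift fails it, so it says nothing about the typical effect.

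The calculations assume equal variances at the two occasions and a shift common to all children. The simulation also assumes normally distributed scores.

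**What to change.** In the Reliability subsection, specify the two-way ICC for absolute agreement, single measurement, and apply the 0.70 mark to it. Report its 95% confidence interval and the mean T1–T2 difference alongside.

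This takes a phrase and a few extra reported numbers from data already to be collected. The cost is that the reported ICC may be slightly lower if there is any shift. If absolute agreement was already intended, the edit only clarifies.
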